**Figure 1 figure1:**
[figure not shown]
Study design schematic for (A) eumenorrheic women with an example 28-day cycle and (B) combined oral contraceptive pill users. Calcium balance represents a urine sample; biochemistry indicates a blood sample; bone health and function represents dual-energy x-ray absorptiometry scan, high-resolution peripheral quantitative computed tomography scan, and EchoLight ultrasound; muscle and tendon function represents muscle strength testing, MyotonPRO, and single-leg drop; and health and lifestyle represents questionnaires.

**Table 1 table1:** Proposed biochemical measurements.

Biochemical measurements		Measurement time points, n		
		EUM^a^ group	COCP^b^ group	Other HCs^c,d^ group
**Reproductive, stress, and metabolic hormones**				
	Estradiol	4	2	1
	Progesterone	4	2	1
	Luteinizing hormone	4	2	1
	Follicle-stimulating hormone	4	2	1
	Testosterone	4	2	1
	Sex hormone–binding globulin	4	2	1
	Cortisol	4	2	1
	Cortisol-binding globulin	4	2	1
	Insulin-like growth factor I (IGF-I)	4	2	1
	IGF-binding protein 1	4	2	1
	IGF-binding protein 3	4	2	1
	Prolactin	4	2	1
	Relaxin	4	2	1
	Free thyroxine (FT4)	4	2	1
	Free triiodothyronine (FT3)	4	2	1
	Thyroid-stimulating hormone (TSH)	4	2	1
	Androstenedione	4	2	1
	Dehydroepiandrosterone sulfate	4	2	1
**Bone**				
	C-terminal telopeptide of type 1 collagen	4	2	1
	Bone–specific alkaline phosphatase	4	2	1
	Amino terminal propeptide of type 1 procollagen	4	2	1
	Osteoprotegerin	4	2	1
	Receptor activator of nuclear factor κβ ligand	4	2	1
**Iron**				
	Hepcidin-25	4	2	1
	Ferritin	4	2	1
	Soluble transferrin receptor	4	2	1
	Hemoglobin	4	2	1
**Vitamin D**				
	Total 25-hydroxyvitamin D (25(OH)D)	2	2	2
	Free total vitamin D (25(OH)D)	1	1	1
	Total 24,25-dihydroxyvitamin D	1	1	1
	1,25-Dihydroxyvitamin D	1	1	1
	Vitamin D–binding protein	1	1	1
	Intact parathyroid hormone	4	2	1
	Phosphate	4	2	1
**Calcium**				
	^44^Ca:^42^Ca ratio	4	2	1
	Albumin-adjusted calcium	4	2	1
	Ionized calcium	4	2	1

^a^EUM: eumenorrheic.

^b^COCP: combined oral contraceptive pill.

^c^HC: hormonal contraceptive.

^d^Other HCs include the hormonal injection, hormonal implant, and hormonal intrauterine system.

All participants will attend a prescreening visit to confirm eligibility and to complete familiarization with the muscle strength and functional movement testing protocols. Thereafter, the EUM group will attend the laboratory on 4 occasions, COCP users will attend the laboratory on 2 occasions, and LARC users on 1 occasion (Figure 1). The first visit for the EUM group will be scheduled on day 2 of the menstrual cycle (ie, the second day of the menstrual bleed), according to the predictions based on their cycle length (see the *Menstrual Cycle Tracking* section). As the predictions may not be exact, the first day of the menstrual bleed will be recorded, and we will accept participant testing between day 1 and day 3 of their menstrual bleed. The second visit will be scheduled at the midpoint between day 1 of the menstrual cycle and predicted ovulation. The third visit will be scheduled to coincide with ovulation, predicted from the first day of menses and then determined in *real time* from a urine test for ovulation (LH stick, Clear Blue Advanced Digital) on the days around predicated ovulation. The final visit will be scheduled between ovulation and menstruation (for a 28-day cycle, day 21) as determined by the fertility tracker. Study visits will be scheduled on days 21 (end of active pill phase) and 28 (end of pill-free week) for COCP users (Figure 1B) and at one point in time for hormonal implant, IUS, and hormonal injection users (not represented in Figure 1).

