### Measurements

#### Menstrual Cycle Tracking

Menstrual cycle phase and length will be monitored in the EUM group; many participants may already be using a menstrual tracking app, which will aid in cycle prediction using historical cycle length data.

Participants will be asked to report day 1 of menses, and all subsequent laboratory visits will be planned according to their reported cycle length. To verify the predicted phases of the menstrual cycle, the EUM group will be given urine dip stick tests (LH surge test) to test for ovulation between days 10 and 15 of the menstrual cycle for a 28-day cycle to ensure that testing occurs during the ovulatory phase. Women will be scheduled for testing at their *predicted* ovulation but will be *actually* tested once they also produce a positive LH test; we expect these dates to coincide. If a woman does not ovulate during the testing cycle, she will be invited to retest the following month.

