#### Venous Blood and Urine Sampling

Venous blood samples will be taken in a resting state after an overnight fast. For the EUM group, blood will be drawn at 4 time points: menses (days 1-3), midfollicular phase (day 7, for women with a 28-day cycle), ovulation phase (day 14 for women with a 28-day cycle), and midluteal phase (day 21 for women with a 28-day cycle). For COCP users, samples will be obtained on day 21 of the pill cycle and the final day of the pill-free week (day 28). LARC users will be tested at a single time point. First-void urine samples will be taken at the same time points as venous blood samples.

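### The article states no rule tying the midluteal visit to the LH-positive day and gives measured progesterone no role in verifying phase, so mistimed or non-luteal samples can enter the day-21 level

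*Protocol article*

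**What the plan says.** The eumenorrheic group has four visits, and the article describes the timing of the last two differently.

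- **Visit 3 (ovulation)** follows an observed event. Menstrual Cycle Tracking says: "Women will be scheduled for testing at their *predicted* ovulation but will be *actually* tested once they also produce a positive LH test". The sticks are used "to test for ovulation between days 10 and 15 of the menstrual cycle for a 28-day cycle".
- **Visit 4 (midluteal)** is described in the visit schedule after Table 1: "The final visit will be scheduled between ovulation and menstruation (for a 28-day cycle, day 21) as determined by the fertility tracker". Menstrual Cycle Tracking adds that "all subsequent laboratory visits will be planned according to their reported cycle length".
- **If predicted and observed ovulation differ**, the article gives no rule for visit 4. It says only "we expect these dates to coincide".
- **If ovulation does not occur**: "If a woman does not ovulate during the testing cycle, she will be invited to retest the following month". The urine LH stick is the only ovulation test described.
- **Progesterone** is listed in Table 1 at four time points for the eumenorrheic group. No section uses it to confirm ovulation or the luteal phase, or to set a sample aside.
- **The model** in Statistical Analyses takes time as the fixed effect, with levels day 1, day 7, day 14 and day 21.

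**The concern.** Primary aim 1 is the effect of cycle phase, so the analysis depends on each sample belonging to the phase it is labelled with. Two kinds of sample could weaken the luteal level.

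1. **Luteal but mistimed.** If visit 4 is set by calendar and the surge comes earlier or later than predicted, the interval from surge to visit varies between women who share the label day 21.
2. **Not functionally luteal.** A positive LH test shows a surge. It does not show that ovulation followed or that a corpus luteum formed. The Introduction itself says that progesterone comes from the corpus luteum after ovulation. An LH-positive cycle without a luteal rise would not trigger the retest rule and would stay in the model as day 21.

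Both tend to pull the luteal mean towards the other phases. With 20 women planned, there is little power to spare at the lower end of the plan's own effect range.

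**Working it through.** **Step 1. Reproduce the plan's sample size, to fix the power formula.** Statistical Analyses gives eta squared 0.06 to 0.14, alpha 0.05, power 0.80, 7 time points and 8 to 17 participants. It gives no correlation; I assume 0.5 and sphericity.

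- f² = eta² / (1 − eta²): 0.06/0.94 = 0.0638 and 0.14/0.86 = 0.1628.
- Noncentrality λ = f² × n × m / (1 − ρ), with df₁ = m − 1 and df₂ = (n − 1)(m − 1).
- With m = 7, eta² 0.06: n = 17 gives λ = 15.19 and power 0.82; n = 16 gives 0.79.
- With m = 7, eta² 0.14: n = 8 gives λ = 18.23 and power 0.86; n = 7 gives 0.79.

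The smallest sizes are 17 and 8, matching the article. The schedule and the model have 4 time points, so m = 4 is used below. The 7 in the sample size text is a separate matter.

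**Step 2. Timing, from the article's own days.** In a 28-day cycle, with a positive LH test on any day from 10 to 15 and a visit fixed on day 21:

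| LH-positive day | Days from LH to visit (21 − LH) | Midpoint of LH day and day 29 |
|---|---|---|
| 10 | 11 | 19.5 |
| 11 | 10 | 20.0 |
| 12 | 9 | 20.5 |
| 13 | 8 | 21.0 |
| 14 | 7 | 21.5 |
| 15 | 6 | 22.0 |

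The interval runs from 6 to 11 days, a spread of 5 days under one label. If menses starts on day 29, day 21 is at most 1.5 days from the midpoint (21 − 19.5) and always lies after the surge and before menses. In this example, timing error makes the luteal sample imprecise; it does not put it in another phase.

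Eligible cycles run from 24 to 35 days, but only the 28-day case is fixed. Two natural extensions of day 21 disagree at the ends of that range:

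- 0.75 × length gives day 18 (24-day cycle) and day 26.25 (35-day cycle).
- Length − 7 gives day 17 and day 28.

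**Step 3. What dilution would cost in the planned test.** Assumptions, none from the article: only the luteal mean differs, ρ = 0.5, n = 20, all 4 visits complete, and a share q of luteal samples carries no luteal effect. The luteal difference is then multiplied by (1 − q), so

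λ = f² × 20 × 4 / 0.5 × (1 − q)² = 160 × f² × (1 − q)², with df 3 and 57 and critical F = 2.77.

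| q | λ, eta² 0.06 | Power | λ, eta² 0.14 | Power |
|---|---|---|---|---|
| 0 | 10.21 | 0.74 | 26.05 | 0.99 |
| 10% | 8.27 | 0.64 | 21.10 | 0.97 |
| 20% | 6.54 | 0.53 | 16.67 | 0.93 |
| 30% | 5.00 | 0.41 | 12.76 | 0.84 |

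This counts only the shrinkage of the mean. It leaves out any added variance from mixing luteal and non-luteal samples.

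**The case against.** **The wording may already imply an LH anchor.** The sentence on visit 4 follows directly on the one that determines ovulation by LH stick, and it places the visit after ovulation. The undefined fertility tracker could be the LH device, since the calendar app is called a menstrual tracking app elsewhere. The statement on reported cycle length also covers visit 3, which the LH result overrides, so planned need not mean final. This stands in part. The article cannot be said to exclude an LH anchor, only to state no such rule. If one is intended, one sentence settles the timing part.

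**A reader might infer that wrong-phase samples are bound to enter.** The article does not support that. Visit 3 requires a positive test, non-ovulating women are invited to retest, and Step 2 shows that day 21 stays between surge and menses in the 28-day example. Samples without a luteal effect would come mainly from LH-positive cycles with no luteal rise, for which the article gives no frequency.

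**A reader might also put a large figure on mistiming.** If the surge differed from prediction by a normal error with SD 2 to 3 days, 32% to 50% of women would be more than 2 days off. That ignores the test window. Cutting the same curve, centred on day 14, to days 10 to 15 leaves 20% to 30%, all early surges and so still post-surge at day 21. The SD is an assumption in either case, and being 2 days off target is not the same as being non-luteal.

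**The damage is limited.** At eta squared 0.14, power holds at 0.84 even with 30% of luteal samples null. The metabolism hypothesis for the cycle concerns the ovulatory phase, and the between-group comparison uses day 14, which is the LH-verified visit. Both points stand. The exposure is in contrasts that involve the luteal level, when the effect is moderate.

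**A progesterone check may sit in a document not shown.** This is fair, and it makes the progesterone part weaker than the timing part. Still, Menstrual Cycle Tracking does set out how phase is verified and when a woman is retested, and names only the LH test.

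**Conclusion.** The point holds as a gap in the visit rules that is cheap to close. The article anchors visit 3 to an observed LH test, states no rule that ties visit 4 to that date, and gives progesterone no verifying role although it is measured at every eumenorrheic visit. Off-midpoint samples, and samples from LH-positive cycles without a luteal rise, can enter the day-21 level and dilute the phase contrast.

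The size is conditional. With 10% to 30% of luteal samples null, power falls from 0.74 to between 0.64 and 0.41 at eta squared 0.06, and from 0.99 to between 0.97 and 0.84 at 0.14. The share, the correlation of 0.5 and the luteal-only pattern of means are assumptions. The 6-to-11-day spread follows from the article's own days if visit 4 stays on day 21.

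**What to change.** **(a) Timing.** State what the fertility tracker is. For remaining participants, schedule visit 4 a fixed number of days after the LH-positive day; the plan's own 28-day example, day 14 to day 21, implies 7 days. Record the LH-to-visit interval for all women, including those already tested.

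**(b) Verification.** Before any outcome model is fitted, prespecify a phase-verified analysis. It leaves out the ovulation and luteal visits of women whose visit-4 progesterone does not exceed the laboratory's follicular reference range. Report it alongside the analysis of all women. When progesterone is itself the outcome, use all women, so that selection is not circular. The planned mixed model already accepts incomplete data.

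**Cost.** No new assay is needed: the LH test and progesterone are already in the plan. Some visits will be rebooked at short notice, and the verified set will be slightly smaller, so it recovers only part of the lost power. Part (a) cannot be applied to visits already completed, and 66 participants had consented when the article was submitted; part (b) still can. No progesterone-triggered retest is asked for, because that would mean repeat visits.

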### Aims and Hypotheses

There is limited evidence for the overarching effects of estrogen on bone and calcium metabolism and musculoskeletal performance and even fewer studies investigating the impact from chronic use of HCs. Our primary aims are to (1) investigate the effect of menstrual cycle phase on bone and calcium metabolism, and musculoskeletal health and performance in EUM, non-HC users (EUM group); and (2) investigate the effects of HC use on bone and calcium metabolism, and musculoskeletal health and function. Our secondary aims are to (1) determine the validity of an ultrasound-based method of measuring hip and spine aBMD compared with “gold standard” DXA and (2) compare calcium and bone metabolism, reproductive hormones, and musculoskeletal function between the pill phase and non-pill phase of COCP use.

This study will test the following hypotheses in 2 study designs. Menstrual cycle phase (within-groups design): (1) calcium and bone metabolism is decreased during the ovulatory phase compared with other phases; and (2) muscle strength and tissue mechanical properties differ across the menstrual cycle. HC use (between-groups design): (1) calcium and bone metabolism is higher in the implant and injection groups compared with IUS (which exerts localized effects) and EUM (ovulatory phase) groups, and lower in the COCP group; (2) estradiol and progesterone are lower in HC users compared with the EUM group during the ovulatory phase; (3) bone macro- and microstructure, muscle strength, and tissue properties are different in HC users compared with the EUM group; and (4) calcium and bone metabolism, reproductive hormones, and musculoskeletal function are different between the pill phase and non-pill phase of COCP use.

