All continuous data will be checked for normality using a Shapiro-Wilk test and by visually checking for skewness and kurtosis. Markers of bone and calcium metabolism, reproductive function, and musculoskeletal health will be compared between contraceptive groups with a one-way between-group analysis of covariance (EUM [day 14] vs COCP [day 21] vs hormonal implant vs IUS vs hormonal injection groups) controlling for age, lean body mass (for bone measures only), physical activity, total 25(OH)D, and previous hormonal injection use. Categorical data from questionnaires will be analyzed using a chi-square test to test for differences between lifestyle, prior HC use, menstrual cycle history, and dietary choices between groups. Nonnormally distributed data will be tested using a Kruskal-Wallis test. Significant main effects of the group will be followed up with post hoc 2-tailed *t* tests with a Bonferroni correction (or Mann-Whitney *U* test for nonparametric data). Paired-sample 2-tailed *t* tests will be used to compare markers of bone and calcium metabolism, and reproductive and musculoskeletal function across the 2 time points in COCP users. Markers of bone and calcium metabolism, reproductive function, and muscle strength and tendon function will be compared between days in the menstrual cycle for the EUM group with a linear mixed effects model with the restricted maximum likelihood estimator to allow incorporation of incomplete data. Time will be the fixed effect (day 1 vs day 7 vs day 14 vs day 21), and a random intercept will be assigned to participants to account for the nonindependence of repeated measures. The significance of the fixed effects from each model will be determined with Sattherwaite degrees of freedom. The normality of the residuals for each model will be checked visually by plotting the residuals against the fitted values and from Q-Q plots. In the event of a significant main effect of time, pairwise comparisons with Holm-Bonferroni corrections and Kerward-Roger degrees of freedom will be used on the linear mixed effects model to identify differences between time points. A Bland-Altman plot will be used to assess the agreement between aBMD measured by ultrasound and DXA. Differences will be considered statistically significant at an α level of *P*<.05 with post hoc *P* values corrected for multiple comparisons.

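### The single untimed IUS visit is compared only with eumenorrheic women at ovulation, so for cycle-sensitive outcomes visit timing could pass for an IUS effect; a supporting analysis would guard against this cheaply

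*Protocol article*

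**What the plan says.** All references are to the protocol article.

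- **Premise about the IUS.** Under Aims and Hypotheses, the first between-group hypothesis is that "calcium and bone metabolism is higher in the implant and injection groups compared with IUS (which exerts localized effects) and EUM (ovulatory phase) groups". The IUS is thus placed beside the EUM group, on the ground that its action is local.
- **Hormone hypothesis.** The second between-group hypothesis is that "estradiol and progesterone are lower in HC users compared with the EUM group during the ovulatory phase". It makes no exception for the IUS.
- **Visit timing.** The visit schedule after Table 1 places the sole visit "at one point in time for hormonal implant, IUS, and hormonal injection users (not represented in Figure 1". Venous Blood and Urine Sampling repeats that "LARC users will be tested at a single time point". Neither gives a cycle day.
- **Phase tracking.** Menstrual Cycle Tracking states that "Menstrual cycle phase and length will be monitored in the EUM group" and that "the EUM group will be given urine dip stick tests (LH surge test) to test for ovulation". No other group is mentioned.
- **Contrast.** Statistical Analyses compares "EUM [day 14] vs COCP [day 21] vs hormonal implant vs IUS vs hormonal injection groups". The covariates are age, lean mass (bone measures only), physical activity, 25(OH)D and previous injection use. There is no term for phase or hormone level.
- **Expected phase effect.** The first menstrual-cycle hypothesis is that calcium and bone metabolism is lower in the ovulatory phase than in the other phases.

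**The concern.** If the IUS acts only locally, a user may still cycle, and a visit on an arbitrary day will usually miss ovulation. Her EUM comparator is measured at ovulation by design. If the protocol's own cycle hypothesis is true and the IUS does nothing systemically, cycling IUS users would still show higher calcium and bone metabolism than the EUM reference.

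The hormone hypothesis is exposed too. Estradiol would tend to look lower in IUS users. Progesterone could look higher, because the Introduction says it is secreted after ovulation and some untimed visits will be luteal.

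At stake is attribution: the trial could report a systemic IUS effect, and set aside its own localized premise, because of visit timing. The issue is confined to outcomes that move with the cycle. DXA and HRpQCT structure should hardly depend on the day of the visit.

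**Working it through.** The plan gives no figure for the IUS-EUM contrast, so there is none to reproduce. The size has to be shown as a range.

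**Inputs from the article**
- 20 women per group, five groups, alpha 0.05, post hoc tests with a Bonferroni correction after a significant group effect.
- The smallest phase effect cited in Statistical Analyses is d = 0.90, for urinary calcium excretion, luteal against follicular. It follows from the figures given: (3.8 − 2.1)/√((1.5² + 2.2²)/2) = 1.7/1.88 = 0.90.

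**Assumptions, not in the article**
- The ovulatory window is 3 days of a 28-day cycle.
- Every other day lies D standard deviations above the ovulatory level. D = 0.9 is borrowed from the luteal-follicular contrast above.
- A fraction q of IUS users still cycles. Non-cycling users are set at the EUM ovulatory level, so that they add no difference.
- Bonferroni covers all ten pairs of five groups: 0.05/10 = 0.005.
- There is no true IUS effect.

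**Spurious difference**
- Chance that an untimed visit falls in the window: 3/28 = 0.107.
- Expected IUS minus EUM = q × D × (1 − 3/28) = 0.89 × q × D.
- At D = 0.9 this is 0.20 SD (q = 0.25), 0.40 SD (q = 0.5) and 0.80 SD (q = 1).
- A 1-day window gives a factor of 0.96, and a 5-day window 0.82.

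**False IUS-EUM finding, 20 against 20, simulated with the phase mixture**

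| D | q | p < 0.05, uncorrected | omnibus gate and p < 0.005 |
|---|---|---|---|
| 0.9 | 0.25 | about 9% | about 1% |
| 0.9 | 0.5 | about 22% | about 5% |
| 0.9 | 1 | about 68% | about 33% |
| 0.5 | 0.25 | – | about 0.7% |
| 0.5 | 0.5 | – | about 1.5% |
| 0.5 | 1 | – | about 6% |

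The right-hand column follows the planned procedure, with the other three groups at the EUM level. The nominal rate for one pair is 0.5%.

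**Where the bias comes from** (cycling IUS users, q = 1). Their expected level is 0.893D above ovulation.
- Against the EUM ovulatory visit: 0.893D, or 0.80 SD at D = 0.9.
- Against a non-ovulatory EUM visit: 0.893D − D = −0.107D, or −0.10 SD.
- Against the plain mean of the four EUM visits, one of them ovulatory: 0.893D − 0.75D = 0.143D, or 0.13 SD.

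**Variance.** With π = q × 0.893, the phase mixture adds D²π(1 − π) to a within-phase variance of 1. At D = 0.9 this is 0.81 × 0.446 × 0.554 = 0.20 at q = 0.5, and 0.81 × 0.893 × 0.107 = 0.08 at q = 1. The gain is modest, so bias is the main issue.

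**The case against.** The strongest reply has four parts.

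- **Continued cycling is only an inference.** It rests on one parenthesis about localized effects. The Introduction describes hormonal contraceptives in general as suppressing ovulation and says hormone-pattern data are lacking in long-acting users. This stands: the article does not say that IUS users cycle, and q is unknown. Recruitment does exclude women reporting amenorrhea or fewer than nine cycles a year without limiting this to one group, but the rule may be meant for the EUM group, and bleeding does not prove ovulation.
- **The shift is borrowed.** A luteal-follicular difference in urinary calcium does not estimate an ovulatory dip in bone markers or the calcium isotope ratio. This stands, so the figures are illustrations.
- **Error rates are modest under the planned tests.** A reader might infer false-positive rates of about 22% to 68% from the uncorrected comparison. The plan requires a significant group effect and a Bonferroni correction, and the rates then fall to about 5% and 33%. Only near-universal cycling with a large dip makes them serious.
- **The timing of the IUS visit is not enough by itself.** A reader might infer that the fault persists whichever EUM visit is the reference. The arithmetic does not support this: the bias nearly vanishes against a non-ovulatory or cycle-averaged reference.

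The reply also notes that LH, FSH, estradiol and progesterone are measured at the IUS visit. That is true, but nothing in the article uses them to time, classify or adjust that visit.

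**Conclusion.** The point holds as a cheap improvement to the analysis. The local-action premise, the untimed IUS visit, tracking in the EUM group alone and an ovulation-only reference do not fit together for cycle-sensitive outcomes. A difference found there could not be attributed to the IUS with confidence.

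The size runs from negligible to material. At an assumed D of 0.9 SD, the false-finding rate is about 1% if a quarter of IUS users cycle, 5% if half do and 33% if all do; at D = 0.5 it is at most about 6%. These figures rest on the 3-day window, the borrowed D, the unknown q and the ten-pair correction.

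The documents do not support reading this as a flaw that invalidates the IUS comparison or requires IUS visits to be rebooked.

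**What to change.** Keep the planned analysis of covariance. For sex hormones, bone and calcium markers, and muscle and tendon tests, pre-specify a supporting IUS-EUM analysis:

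- **(a)** Compare IUS users with each EUM woman's mean over her four visits. The plain mean gives ovulation a weight of 1/4, so a small remainder of 0.143D is left for cycling users.
- **(b)** Classify each IUS user's likely phase, or suppression, from the LH, FSH, estradiol and progesterone already measured at her visit, with the date of last bleed where one is on record. Compare her with the matching EUM visit.

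Claim a systemic IUS effect on these outcomes only if the difference persists. Leave DXA and HRpQCT outcomes as planned.

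The cost is one analysis rule, with no new visit or assay. The limits are that one hormone sample classifies phase imperfectly, matched subsets of a group of 20 are small, and splitting by cycling status conditions on something the IUS may change. Part (b) is therefore supportive only. LH-timed booking is not needed: it would also condition on ovulation, and it would reach only women not yet tested.
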